### Randomization and blinding

Eligible participants who have provided informed consent, either on behalf of themselves, by proxy (parents) or both, are randomized to either injections of BoNT-A or saline. The randomization will be performed using prerandomized lists at the four study centers, made by the unit of Applied Clinical Research at the Norwegian University of Science and Technology, using a web-based randomization system, including stratification for age (4–10 years and 11–17.5 years) and study center. The randomization lists are distributed to, and stored at, each respective study site’s pharmacy department which allocates the participants to either BoNT-A injections or saline (allocation ratio 1:1). The appropriate solution of BoNT-A or saline will then be prepared at the pharmacy and delivered in syringes to the researchers. In a pilot, we found that the two solutions were indistinguishable regarding smell and appearance. Accordingly, trial participants and their caregivers, and all other persons involved in treatment and outcome assessment are blinded to group allocation. The procedure for emergency unblinding is included in the study’s Trial Master File (TMF) and will be carried out by the responsible pharmacy in cooperation with coordinating national investigator of the study.

### Treatment procedure

The dosage of BoNT-A (Botox®; Allergan) used in this study is based on one systematic review [23], one original paper [24] and two international expert consensus papers [25, 26]. The total maximum body dose of Botox® will be 420 Units. Maximum dose per injection site will be 50 Units. The gastrocnemius muscle will receive 5–6 Units Botox® per kilogram, with a maximum of 180 Units in each leg. The soleus muscle will receive 2 Units Botox® per kilogram with a maximum dosage of 60 Units in each leg. The maximum injected volume per injection site will be 0.5 ml of a solution of 100 Units of Botox® in 1 ml 0.9% saline, or 0.9% saline only (placebo). The placebo dose will be the same dose in milliliters as the reconstituted Botox®. The injections are given using ultrasound-guidance, allowing quick visual identification of the target muscle and exact localization of the needle in the desired position. The participants will receive the treatment using local anesthesia and conscious sedation with oral or nasal benzodiazepines if desired by the participants and their caregivers. The sedation procedures will be given in accordance with standard guidelines used in each of the participating centers.

### Study visits

Flow of participants and the timeline is presented in Fig. 1. The primary endpoint will be 12 weeks post injection, when a clinical effect can be expected. Outcomes at 4 and 24 weeks post injection will also be evaluated in order to control for the specific paralyzing effect on the muscle [27] and a possible delayed functional effect [15], respectively. Thus, the outcome measures will be assessed at baseline and 4, 12 and 24 weeks after injections (Fig. 1: P1, P2 and P3).

**Fig. 1 Fig1:**
[figure not shown]
Flow of participants through study. Figure 1 shows the flow of participants through the study according to the Consolidated Standards of Reporting Trials (CONSORT) guidelines

At each visit, there will be a face-to-face session with the child and the parents to map the period from the last visit. In addition, any AE will be recorded in the eCRF, and action taken according to procedure included in the TMF. All changes in concomitant medication (including vitamins, herbal preparation and other “over-the-counter” drugs) used by the patient will also be recorded in eCRF. Moreover, the content and intensity of supportive therapy, such as specific exercise programs, physiotherapy and ankle-foot orthoses (AFO) will be recorded in detail. Since such supportive therapy is not standardized in Norway and, therefore, will vary between centers according to their clinical guidelines, stratification by center at randomization is made.

At baseline, the following subject characteristics are reported: GMFCS level, CP distribution (uni/bilateral) number of previous BoNT-A treatments in calf muscles, previous surgeries to the lower limbs, age and gender. At each visit, spasticity is evaluated using the clinical Tardieu Test [28], and weight and height are also registered.

### Primary outcome measure

The primary outcome measure is energy cost (EC) in J/kg/m during walking, obtained from a 5-Minutes Walk Test (5MWT) at a self-chosen comfortable speed [29] with simultaneous gas-exchange measurements [3]. It has been reported that children with CP have an EC during walking corresponding to 6.84 J/kg/m (standard deviation (SD) 2.0 J/kg/m) and that the smallest detectable difference of this measure is 0.464 J/kg/m (or 6.8%) [29]. Taking this information into consideration we defined a 10% improvement in the intervention group (i.e., 0.684 J/kg/m) to be clinically significant. For children using an AFO on a regular basis, this assessment will be carried out both with and without the orthosis.

### Secondary outcome measures

Secondary outcomes are:Walking capacity, reflected as (a) distance walked during a 1-Minute Walk Test (1MWT) where the participant is walking as fast as possible without running [30] and (b) perceived exertion during walking assessed by the use of the OMNI Rating of Perceived Exertion scale (OMNI-RPE), measured after the 5MWT at comfortable speed and after the 1MWT [31]. In the OMNI-RPE the children are asked to rate their perceived exertion on a 10-point scale (0–10) by the use of a series of four pictures of a child walking up a hill becoming progressively more and more tired. It is validated for children with CP [31]Habitual physical activity, measured by two body-worn accelerometers (Axivity Ltd.); one at the thigh and one at the lower back, over a period of seven consecutive days following visits at baseline, and at P1, P2 and P3. The accelerometer as a measure of habitual physical activity is reported to be feasible in children with CP [32] and valid in reflecting time in sitting, lying, standing and walking [33]. In our study, two accelerometers are used in order to differentiate between sitting and lyingPerceived change in performance and satisfaction, measured by The Canadian Occupational Performance Measure (COPM). The COPM is used to detect changes in self-perceived activity performance in the areas of self-care, productivity (i.e., school) and leisure. At baseline, the instrument will be administered as a semistructured interview that focuses on activities that the participant wants, needs or is expected, to perform. Through the interview, the child will be allowed to identify and prioritize up to three “problems” related to gross motor function. Performance and satisfaction related to each problem are then scored on a 10-point ordinal scale (1–10), where a higher score reflects greater performance and satisfaction, respectively. Rescoring will be made at P1, P2 and P3. The COPM in its original version, as well as in the Norwegian translation, has been found to be a valid, reliable and responsive outcome measure ranging from satisfactory to excellent [34]Pain during the last 2 weeks will be assessed stepwise. Participants will be asked to record all pain sites on the body outline from the Brief Pain Inventory (BPI), the Norwegian version [35] and to respond to the two questions on pain (“how much” and “how often”) from the Child Health Questionnaire (CHQ, Norwegian version) [36]. To capture the level of pain interference with function, pain interference with the three BPI items general activity, walking and sleep will be recorded on 0 (no interference) to 10 (complete interference) rating scales. In cases of calf pain, identical recordings will be made for the right and left leg separately and the child will be asked to indicate maximum calf pain intensity on the Faces Pain Scale-Revised (FPS-R) [37]. To secure the view from both parents and the young people with CP separately, parents will respond to a questionnaire while their child is occupied with test procedures, and the young people with CP will give their responses in an interview.

In addition, at all four visits, spasticity in the calf muscles will be assessed by the clinical Tardieu Test [28] and passive range of motion in the ankle joint will be measured by a manual goniometer. Moreover, during the 5MWT and the 1MWT, concurrent heart rate monitoring and accelerometry will be obtained. All data collection will be carried out by trained assessors and pilots on all outcomes were made before trial start. Collected data will be entered on site into each participant’s eCRF by the assessors and the data will be checked by the data manager in the study after each entry.

### Sample size and power

Sample size calculations were performed for a two-sample (two-sided) *t* test for comparing the change in the primary outcome measure, EC, from baseline to 12 weeks post intervention between the two groups. The estimate was based upon a mean difference in change of 0.684 6.84 J/kg/m [29]. The SD of change was set at 1.0 based on other intervention studies [3, 38], in which the SD of change is found to be approximately half of the baseline SD [29], and assuming a baseline SD of 2.0 J/kg/m [29]. Thus, to detect a clinical significant improvement in the primary outcome, measure, reflected as a 10% decrease in EC (from 6.84 J/kg/m), with a power of 80%, using a two-sided *t* test and a 5% significance level, a sample size of 32 children/adolescents per group is necessary. Allowing for a dropout of 30%, 48 children/adolescents are needed. In practice, the test will be performed as a post-hoc test for a linear mixed model (LMM), but the sample size calculation for the *t* test for the change from baseline to post is assumed to be conservative in that respect.

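### The stated 32 per group gives 76.8% power for the named t test, not 80% (35 are needed); the 48 randomised per group gives about 79% at the planned dropout

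*Protocol article*

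**What the plan says.** The section *Sample size and power* of the protocol article gives a complete set of inputs:

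- Test: "Sample size calculations were performed for a two-sample (two-sided") *t* test of the change in energy cost from baseline to 12 weeks.
- Error rates: "a 5% significance level" and "with a power of 80"%.
- Effect: "The estimate was based upon a mean difference in change of 0.684" J/kg/m, which is 10% of 6.84.
- Variability: "The SD of change was set at 1.0 based on other intervention studies".

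From these it concludes that "a sample size of 32 children/adolescents per group is necessary", and then: "Allowing for a dropout of 30%, 48 children/adolescents are needed". The 48 must be per group, because the abstract and the registration table give a total of 96 with 1:1 allocation. The section adds that the real test will be a contrast from a linear mixed model, for which the t-test calculation is assumed to be conservative.

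The section *Primary outcome measure* introduces the same number in different terms: "we defined a 10% improvement in the intervention group (i.e., 0.684 J/kg/m) to be clinically significant". The section *Statistical analysis* reports the effect as the between-group mean difference in change to 12 weeks, with a 95% confidence interval.

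**The concern.** Every input is printed, so the output can be checked, and 32 does not come out. Nor does 48 follow from 32 at the stated dropout rate. A reader who takes 32 completers per group as the number needed for 80% power would think the trial still adequately powered at a level of attrition where it falls about three points short. That matters most if the result is null or borderline and power is used to interpret it.

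There is a smaller point of wording. The 0.684 is described once as an improvement in the intervention arm and then used as a difference between arms. The two agree only if the placebo arm is taken not to change, which the article does not say.

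**Working it through.** **Inputs** (all from *Sample size and power*): difference δ = 0.684; SD of change σ = 1.0; two-sided α = 0.05; power 0.80; equal groups.

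**1. Attempt to reproduce 32 by the normal approximation.**
n = 2σ²(z₀.₉₇₅ + z₀.₈₀)² / δ² = 2 × (1.960 + 0.842)² / 0.684² = 2 × 7.849 / 0.4679 = 33.55, so 34 per group. Power at 32 is Φ(0.684 × √(32/2) − 1.960) = Φ(2.736 − 1.960) = Φ(0.776) = 78.1%.

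**2. The test that the article names.** For the two-sample t test, power comes from the noncentral t distribution with 2n − 2 degrees of freedom and noncentrality (δ/σ)√(n/2). Solving for 80% gives n = 34.54, so 35 per group.

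| Completers per group | t test | Normal approximation |
|---|---|---|
| 32 | 76.8% | 78.1% |
| 33 | 78.1% | 79.3% |
| 33.6 | 78.9% | 80.1% |
| 34 | 79.4% | 80.5% |
| 35 | 80.5% | 81.6% |

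Neither method returns 32. A one-sided normal calculation gives 27. Reaching 32 takes a difference of about 0.71 or an SD of about 0.96 to 0.97, and the article states neither.

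**3. Dropout.**
- From the stated 32: 32 / 0.70 = 45.7, so 46. Multiplying instead, 32 × 1.3 = 41.6, so 42. Neither is 48.
- From the t-test figure: 35 / 0.70 = 50 per group.
- From the unrounded normal figure: 33.55 / 0.70 = 47.9, so 48. This route does give the printed enrolment target.

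**4. What the planned enrolment delivers.** 48 × 0.70 = 33.6 completers per group, and the t-test power is 78.9%. Keeping 35 completers out of 48 allows dropout of 1 − 35/48 = 27.1%.

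**5. Possible gain from baseline adjustment.** This needs an assumption that the article does not make, namely that the SD is 2.0 at 12 weeks as well as at baseline. An SD of change of 1.0 then implies 1.0² = 2 × 2.0² × (1 − ρ), so ρ = 0.875. The adjusted SD is 2.0 × √(1 − 0.875²) = 0.968. Power is 81.4% at 33.6 completers and 79.5% at 32.

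**The case against.** The strongest reply is that the number governing recruitment is 48 per group, and that it stands up. It follows from the stated inputs by the normal approximation without intermediate rounding, and it misses 80% by only about one point under the exact t test. That the authors worked this way is an inference, but the arithmetic is right. It limits the finding: the faulty figure is the intermediate 32, and the 76.8% applies at 32 completers, not at the planned enrolment and dropout.

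The article also says that the t-test calculation is conservative for the mixed model, which uses all four visits and retains partial data. That is reasonable, and under the equal-SD assumption above the planned enrolment exceeds 80%. But the article neither quantifies the gain nor states the assumption, and a gain in a different analysis does not make 32 the right answer for the t test.

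On the wording of 0.684, a reader might infer that a 10% fall in the botulinum toxin arm could be declared clinically significant whatever happened on placebo. The article does not support that. The sample size and analysis sections both fix the effect as the between-group difference in change, its 95% confidence interval is already planned, and no rule declares clinical significance from one arm alone. Nor is it established how 32 arose. Rounding the difference to 0.70 does not explain it cleanly, since the normal formula then gives 32.04, which rounds up to 33.

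**Conclusion.** The sample size statement is wrong on its own inputs: 35 completers per group are needed for 80% power by the named t test (34 by the normal approximation), and 32 gives 76.8% (78.1%). The step from 32 to 48 is also wrong as printed. The practical size is small. At 48 randomised per group and 30% dropout the t test has about 79% power, and 80% holds up to about 27% dropout. These figures rest only on the article's difference of 0.684 and SD of change of 1.0. The figure of about 81% with baseline adjustment further requires SDs of 2.0 at both visits. A reader might infer that the trial is materially underpowered or that enrolment must rise; a shortfall of about one point at the planned enrolment supports neither. The two descriptions of 0.684 are a wording mismatch that leaves the arithmetic and the planned effect measure unchanged.

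**What to change.** In *Sample size and power*, replace 32 with 35 completers per group. State that 48 randomised per group gives about 79% power by the two-sided t test at 30% dropout, and 80% up to about 27% dropout. If the mixed model or baseline adjustment is cited as recovering the difference, give the figure together with its assumption (about 81% if the baseline and 12-week SDs are both 2.0).

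In *Primary outcome measure*, describe 0.684 J/kg/m as the between-group difference in change, as the sample size section already uses it. The full analysis plan, which the article says will be made before unmasking, can carry the same definition.

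The cost is wording only: the stated power becomes about one point less favourable, and enrolment and analysis stay as planned.

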### Statistical analysis

The statistical analysis for the primary aim will be performed using a LMM including data from baseline and 4, 12 and 24 weeks post intervention. The test for difference in change in the primary outcome measure from baseline to 12 weeks between the treated and placebo group will be done using a post-hoc test following the LMM. Age, GMFCS level, number of prior BoNT-A treatments and study center will be considered as potential covariates. A similar model will also be used to study the secondary outcome measures. The LMM handles missing data for the outcome measure. Nonparametric tests will be used to test for a between-group difference in change score for secondary outcome measures expressed with ordinal data, and for scalar data in case the requirements for the parametric tests are not met. The effect size will be expressed as mean difference between the groups in change from baseline to 12 weeks with a 95% confidence interval.

In addition to investigating the independent effect of BoNT-A on walking, the associations between the change scores of the primary and secondary outcome measures will also be studied.

The level of significance is set to 0.05 and no formal adjustments for multiple testing will be carried out.

A complete plan for the analyses of the outcome measures will be made before unmasking group adherence. Results will be reported according to the Consolidated Standards of Reporting Trials (CONSORT) Statement [39].

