We hypothesize that injections of BoNT-A in the calf muscles will reduce EC during walking, improve walking capacity, increase habitual physical activity and reduce pain. Moreover, we hypothesize that injections with BoNT-A will improve perceived performance and satisfaction related to ambulation. Secondary, we hypothesize that younger children and children with lower gross motor function will improve more in EC than older children and children with greater gross motor function.

In a substudy of this RCT, we aim to identify different CP phenotypes of responders to BoNT-A treatment and, moreover, to gain insight into the processes underlying BoNT-A-induced changes in walking. On that account, we want to identify gait and muscle activation patterns, spasticity and strength characteristics related to the response of BoNT-A on our primary and secondary outcome measures. Moreover, semistructured qualitative interviews will be conducted on a subset of participants (minimum 25) and their parents. Details of these studies are not presented in this paper.

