This current trial has several strengths. The study is comprehensive, including a relatively homogenous population of children classified with GMFCS levels I and II. Moreover, the intervention comprises single-level injections in the calf muscles only. Including participants with multilevel injections as well would challenge the interpretation of the results. Finally, the evaluation of effect is comprehensive and includes objective standardized tests and measures on both the impairment and activity level according to the ICF [42]. Effect on participation is not evaluated explicitly, since we consider that the follow-up time of 24 weeks will be too short to expect significant clinical changes in this dimension. Nonetheless, the COPM may give some indications of possible effects on participation.

The randomization procedure is stratified according to age and study center. The age range of the participants is quite wide, from 4 years to 17.5 years. Since there is possibly an effect of age, due to assumed structural and functional changes in the muscle as a result of growth and spasticity [43], two age groups are created (4–9 and 10–17.5 years) to make sure that age is evenly distributed among BoNT-A and placebo groups. The differences between the study sites regarding supportive therapy will be controlled through the stratification of the randomization. Moreover, the detailed description of this therapy applied to each participant will enable us to correct for potential differences in supportive therapy.

A main challenge in the project is recruitment of participants; the patient base is small, and the possibility of receiving placebo may cause some reluctance to participate. In case of slow recruitment, we plan to implement one more study site in a fourth health region in Norway.

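### The primary model leaves the randomisation strata optional and baseline handling open; one form it permits gains nothing over the change-score t test

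*Protocol article*

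**What the plan says.** - **Strata.** The Discussion states: "The randomization procedure is stratified according to age and study center". The age groups are given in two ways. Randomization and blinding has "including stratification for age (4–10 years and 11–17.5 years) and study center"; the Discussion has "two age groups are created (4–9 and 10–17.5 years".
- **Covariates.** Statistical analysis says: "Age, GMFCS level, number of prior BoNT-A treatments and study center will be considered as potential covariates". The two strata sit beside two factors that are not strata. No rule for inclusion is given, and nothing says whether covariates enter as main effects or by visit.
- **Baseline and primary test.** The analysis is described as "using a LMM including data from baseline and 4, 12 and 24 weeks post intervention", so baseline is itself one of the modelled outcomes. The primary comparison, made as a contrast after the model is fitted, is worded as "The test for difference in change in the primary outcome measure from baseline to 12 weeks between the treated and placebo group". Baseline energy cost is not named as a covariate, and nothing says whether the arms share a baseline mean.
- **Role given to stratification.** The Discussion says: "The differences between the study sites regarding supportive therapy will be controlled through the stratification of the randomization". The sentence after it adds that the therapy recorded for each child will allow correction for differences.
- **Sample size.** Sample size and power uses a two-sided t test on change, with difference 0.684, SD of change 1.0, 80% power and 5% significance. It arrives at 32 per group, and 48 after 30% dropout. It assumes that this calculation is conservative relative to the mixed model.
- **Deferral.** A complete analysis plan is promised before group allocation is unmasked.

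**The concern.** Stratified allocation balances age and centre between the arms. It does not by itself take the variation between strata out of the standard error; the model has to do that. The article expects a possible age effect and says that supportive therapy varies by centre, so it gives its own reasons to think that the strata may predict outcome. It still leaves their inclusion to choice.

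The second issue is less visible. When baseline is an outcome and the test is a change contrast, the listed covariates may do no work even if they are included, and the information in baseline energy cost may not be fully used. The mixed model would then not have the advantage over the t test that the sample size section counts on. What is at stake is precision, in a trial whose Discussion calls recruitment a main challenge. Bias and false-positive risk are not at issue.

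**Working it through.** **1. The plan's own figure.** Inputs from Sample size and power: difference 0.684, SD of change 1.0, two-sided 5%, power 80%.

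n per arm = 2 × (1.960 + 0.842)² × 1.0² / 0.684² = 33.55, rounded up to 34. The exact noncentral t calculation gives 35. The stated 32 is close but slightly low; its power is 78.1% (normal approximation) or 76.8% (exact t). The 48 follows from 33.55 / 0.7 = 47.9; from 32 it would be 32 / 0.7 = 45.7, so 46.

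**2. What main effects do to the contrast.** Write energy cost for child i in arm a at visit t as μ(a,t) + x(i)β + e(i,t), with μ free for every arm and visit and x constant over time. The change from baseline to 12 weeks is μ(a,12) − μ(a,0) + e(i,12) − e(i,0). The term x(i)β cancels. On complete data the estimate is the plain between-arm difference in mean change.

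**3. Numerical check.** Mixed models with unstructured covariance were fitted to 25 simulated data sets per setting (64 children, four visits). Covariates were age group, centre and GMFCS level, entered as main effects.

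| Setting | Mean SE, no covariates | Mean SE, main effects | Largest shift in estimate |
|---|---|---|---|
| Free baseline means, complete data | 0.2329 | 0.2329 | below 1e-12 |
| Free baseline means, about 30% dropout | 0.2477 | 0.2475 | 0.055 J/kg/m |
| Common baseline mean, complete data | 0.2246 | 0.2230 | 0.136 J/kg/m |

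In one complete data set, the free-means contrast and the simple difference in mean change were both −0.8047. Without covariates, a common baseline mean lowers the SE by 1 − 0.2246/0.2329 = 3.6%, or about 7% in variance.

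**4. Size of the baseline gain.** The article gives baseline SD 2.0 and SD of change 1.0. The 12-week SD is not given; take 2.0 as an assumption.

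- Correlation: (2.0² + 2.0² − 1.0²) / (2 × 2.0 × 2.0) = 0.875.
- Residual variance after baseline adjustment: 2.0² × (1 − 0.875²) = 0.9375, against 1.0 for change. This is a cut of 6.25%; the SD goes from 1.0 to 0.968.
- n per arm: 33.55 × 0.9375 = 31.46, so 32 instead of 34.
- Power at 32 per arm: 78.1% to 80.7% (normal), 76.8% to 79.4% (exact t).
- Power at 48 × 0.7 = 33.6 per arm: 80.1% to 82.5% (normal), 78.9% to 81.4% (exact t).

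The result depends on the assumed 12-week SD:

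| 12-week SD | Correlation | Residual variance (change = 1.0) |
|---|---|---|
| 1.6 | 0.869 | 0.63 |
| 1.8 | 0.867 | 0.81 |
| 2.0 | 0.875 | 0.94 |
| 2.2 | 0.891 | 1.00 |
| 2.4 | 0.913 | 0.96 |

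**5. Strata.** The article gives no figure for how much of the variance in change age and centre explain. For illustration only, let that share be R². With balanced strata left out of the model, the true two-sided alpha is 2 × (1 − Φ(1.96 / √(1 − R²))): 4.4% at R² = 0.05, 3.9% at 0.10 and 3.4% at 0.15. The direction is always conservative.

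**The case against.** The strongest reply is that the article fixes neither main effects nor free baseline means. A model with a common baseline mean, or with covariates by visit, fits the same sentences and recovers the information. The article also condenses a fuller protocol and promises a complete plan before unmasking, where such details normally sit. This stands in large part. A reader might infer that precision is certainly lost, or that covariates will be picked by result; the documents support neither. What remains is that the article does make a statement about covariates, and that statement leaves optional the two factors on which the design balanced.

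Other points that stand:

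- Exact cancellation needs complete data, and 30% dropout is planned. With dropout the mixed model also uses partial follow-up that a completers' t test discards, so the assumption that the t test is conservative may have some support there. Main-effect covariates still left the mean SE almost the same.
- The baseline gain is modest, and close to nil at a 12-week SD of 2.2.
- Omitting the strata creates no false-positive risk, and any power loss is relative to a better model.
- The Discussion does not rely on stratification alone, since it also mentions correction using recorded therapy.
- GMFCS level is not a stratum, so the design does not require adjusting for it.

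One might also infer that the covariate sentence fails the secondary hypothesis, "we hypothesize that younger children and children with lower gross motor function will improve more in EC than older children". That is a separate point: testing it needs treatment-interaction terms, and the covariate sentence does not claim to provide them.

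**Conclusion.** The point holds as a conditional one. The wording permits a primary model in which the listed covariates leave the 12-week change contrast unchanged on complete data, and almost unchanged in SE with about 30% dropout. On complete data that model is no more precise than the change-score t test, so the assumption that the sample size is conservative gains no support there.

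If the 12-week SD equals the baseline SD of 2.0, the avoidable loss from not adjusting for baseline is 6.25% of variance, about 2.5 power points or 2 children per arm. For a 12-week SD of 1.6 to 2.4 the loss runs from about 37% of variance to almost none. The further loss from omitting age and centre cannot be quantified from the article and acts only in the conservative direction. Validity is not threatened. This is an improvement worth making because it uses data already collected.

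**What to change.** First reconcile the age cut-offs (4–10 and 11–17.5 years against 4–9 and 10–17.5 years) by stating which grouping the randomisation lists used; until then the stratum to adjust for is not defined. Then state in the protocol or the promised analysis plan, before unmasking:

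- The primary mixed model uses energy cost at all four visits with the arms constrained to a common baseline mean. Equivalently, post-baseline energy cost is the response and baseline energy cost is a covariate interacted with visit. The primary test is the treatment effect at 12 weeks.
- Age stratum and centre are always in the model, each interacted with visit, with no data-driven selection.
- Adjustment for GMFCS level or prior treatments is optional, but is decided in advance.

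The cost is wording and a few degrees of freedom. With four centres, age and centre take 1 + 3 = 4 terms per visit, so 12 over the three post-baseline visits (16 if baseline is modelled too), against about 96 × 0.7 = 67 completers. By-visit terms do not pay off if the strata do not predict change. In simulated complete data of that kind, with unstratified allocation and GMFCS level included as well, the spread of the free-means estimates rose from 0.231 to 0.250. That rests on only 25 data sets, and stratified allocation should reduce the cost.
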